### Additional variables

For the purposes of sample description, we collect data on demographic variables such as maternal age, education, occupation, parity, and current use of psychosocial services (e.g., social worker, support groups). Infant illness severity is assessed with the Revised Nursery Neurobiologic Risk Score (NBRS) [62]. It includes 7 items that assess the presence, severity and duration of medical events associated with the risk of later abnormal neurodevelopment for the infant. The NBRS is scored following a review of the infant's medical record. NBRS scores correlate with later child neurological examination scores [63], as well as with poorer subsequent social, cognitive and psychomotor development of children born VLBW [64-66]. At the time of discharge, the NBRS is scored by a rater blind to the mother's group assignment.

We are also collecting data for exploratory analyses of two important outcome variables:

1. Maternal depression is assessed using the Edinburgh Postnatal Depression Scale (EPDS)[67]. This 10-item scale is designed to screen for postpartum depression in community samples. The items are rated on a scale from 0 to 3, and refer to symptoms experienced in the past 7 days. Respondents who score above the cut point of 12 are classified as at risk for a depressive disorder. The split-half reliability of the scale is 0.88, and the standardized alpha coefficient is 0.87. In validation studies, using a cut score of 12, the EPDS was found to have a sensitivity of 68% to 95%, and a specificity of 78% to 96%, when compared to a diagnosis of major depression made by psychiatric interview [68-70].

2. Bayley Scales of Infant Development, 3^rd ^edition (BSID-III, 2005) [71] are used to gather pilot data on infant cognitive development. This is the most recent revision of a widely used measure of infant development, and consists of 5 scales: cognitive, language, motor, social-emotional, and adaptive. This instrument has excellent psychometric properties, and has been validated on over 1700 children.

Given that maternal depression is a dichotomous outcome, the sample size required to adequately test any related hypotheses would be prohibitive. Similarly, the trial is not adequately powered to test differences between the experimental and control groups in terms of infant developmental outcome on the BSID-III. Although we cannot test hypotheses related to these variables, the pilot data that we are collecting on these variables will help with future projects in this area.

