### Trial interventions

The experimental "Cues" intervention consists of 6 sessions to teach mothers to: 1) read their own cues and recognize signs of anxiety/distress, 2) utilize various strategies to reduce their distress, including muscle relaxation, imagery, and cognitive reframing, 3) read their infant's communication cues, and 4) respond sensitively to infant cues and distress. In the first two sessions, the intervener explains the relationship between thoughts, feelings, and behaviour, and teaches mothers how to identify negative automatic thoughts. Participants acquire skills that help them to relax and to counteract maladaptive thought patterns. The next two sessions focus on understanding the behaviour of VLBW infants, identifying infant states cues and learning how to interact sensitively with the infant. The fifth session is devoted to mother-infant interaction during feeding. Each teaching session lasts 60 – 90 minutes. There is also a telephone follow-up call, to review the techniques that have been taught and to maintain contact with participant mothers. The first 5 sessions take place in the NICU at a frequency of 1–2 sessions per week. The last session takes place in the mother's home 2–4 weeks after discharge. Total dose is 9–10 hours.

The program is delivered in one-on-one sessions between the mother and an intervener. Group sessions are not feasible because mothers differ greatly in the timing and frequency of their NICU visits; moreover, other studies with postpartum women report a high level of non-compliance with group interventions [54]. Prior to each session, the mother is given a booklet describing the main ideas to be discussed at that session, and is asked to read the booklet before meeting with the intervener. Learning exercises are also included to assist mothers to apply the content to their own experience.

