### Planned analyses

No interim analyses are planned. Upon completion of the study, we will compare baseline values for demographic variables to assess the adequacy of randomization. These include maternal age, education, parity, psychosocial services used by the mother, and infant illness severity. The primary outcome is the difference in STAI scores between the intervention group and the control group, evaluated immediately post-intervention. This is a continuous measure and will be analyzed using an unpaired t-test (i.e. comparison of scores between two independent samples) and an intent-to-treat strategy. The overall significance level will be considered at a two-sided 0.05 level. As a secondary analysis, we will use a multiple regression model to account for other predictors of outcome, including baseline STAI, and the demographic variables noted immediately above. Finally, as an exploratory analysis, we will compare groups based on actual treatment received in addition to our primary intention-to-treat analysis. The analysis of secondary measures will proceed in a likewise fashion. We will also report on contamination and describe other services used during and after the intervention. Because we only have 46 subjects per group, we cannot use sophisticated multiple imputation techniques to estimate expected results in subjects who withdraw from the study. Therefore, we will document and describe the reasons for attrition within each group, but exclude these subjects from the multiple regression analyses.

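### Infant illness severity is used as a baseline check and regression covariate, but the NBRS behind it is scored at discharge, after randomization and five of six sessions

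*Protocol article*

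**What the plan says.** On the timing and content of the score, Additional variables in the protocol article says "At the time of discharge, the NBRS is scored by a rater blind" to allocation. Of the instrument it says: "It includes 7 items that assess the presence, severity and duration of medical events". It names no other measure of infant illness severity and gives no date after which events stop counting.

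On its use, Planned analyses says "we will compare baseline values for demographic variables to assess the adequacy of randomization" and continues: "These include maternal age, education, parity, psychosocial services used by the mother, and infant illness severity". The secondary multiple regression then takes predictors "including baseline STAI, and the demographic variables noted immediately above", which brings illness severity into the model. The secondary measures are to be analysed by the same approach.

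On the order of events, Procedures names the STAI, PPQ and EPDS as the measures taken before randomization; the NBRS is not among them. Trial interventions adds: "The first 5 sessions take place in the NICU". The sixth session is at home after discharge.

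**The concern.** A variable that serves as a baseline check or as an ordinary covariate in a randomized comparison should be fixed before allocation. This one is not. Two uses are affected, in different ways.

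- **Balance check.** An arm difference in a discharge score may reflect allocation or anything that happened between allocation and discharge. A reader of the baseline table could take a later difference for failed randomization.
- **Adjusted models.** If the programme alters the infant's hospital course, the discharge score lies partly downstream of treatment, and holding it constant changes what the treatment coefficient estimates. If Cues lowered the NBRS and a higher NBRS went with higher maternal anxiety, adjustment would take away part of the benefit.

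At stake are the reading of the baseline table and of the adjusted secondary analyses.

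**Working it through.** **Step 1: order of events** (Procedures, Trial interventions, Additional variables)

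1. Consent, then STAI, PPQ and EPDS.
2. Randomization; an intervener makes contact within a day.
3. Sessions 1 to 5 in the NICU at one to two per week, so 5/2 = 2.5 to 5/1 = 5 weeks.
4. Discharge; NBRS scored from the chart.
5. Session 6 at home, 2–4 weeks after discharge.
6. Post-intervention STAI, 2–3 weeks after the intervention ends.

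The score comes after randomization and after 5/6 = 83% of the planned sessions.

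**Step 2: balance check**

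Write the observed arm difference in discharge NBRS as D = D_pre + D_post, split at randomization. Only D_pre bears on allocation, and only D is observed.

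- If arm has no effect on the score, D_post is noise. A 5% test keeps its error rate, but a difference cannot be traced to allocation.
- If arm shifts the score by δ SD, the chance of a significant difference in the direction of the shift, with 46 per arm and sound randomization, is Φ(δ√(46/2) − 1.96). This is 0.025 at δ = 0, and 0.069, 0.158 and 0.301 at δ = 0.1, 0.2 and 0.3. These shifts are assumptions.

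**Step 3: STAI SD**

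The article gives 7 points, alpha 0.05 two-sided, power 0.8 and 40 per group, but no SD. The 40 can therefore only be solved backwards:

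- SD = Δ√(n/2) / (z₀.₉₇₅ + z₀.₈₀) = 7 × √20 / (1.960 + 0.842) = 11.17.
- The t-test version gives 11.04.
- Run forward with the normal formula, SD 11 needs 39 per group and SD 12 needs 47.

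I use 11.

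**Step 4: bias in the adjusted difference**

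For a linear model, bias ≈ δ × β × SD. Here δ is the shift in NBRS caused by the arm (SD units) and β is the standardised NBRS-to-STAI slope given the other covariates. Neither is in the article; I assume δ from 0 to 0.3 and β from 0 to 0.4.

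- δ = 0 or β = 0: 0 points.
- δ = 0.1, β = 0.2: 0.1 × 0.2 × 11 = 0.22 points (0.22/7 = 3% of the 7-point target).
- δ = 0.2, β = 0.3: 0.2 × 0.3 × 11 = 0.66 points (9%).
- δ = 0.3, β = 0.4: 0.3 × 0.4 × 11 = 1.32 points (19%).

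With β capped at 0.3 and SD 11.2, the upper end is 0.3 × 0.3 × 11.2 = 1.01 points (14%).

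**The case against.** The strongest defence is that a programme teaching mothers anxiety management and sensitive interaction may do little to an infant's medical events, so the discharge NBRS may in practice act like a prognostic covariate. Participants excludes highly unstable infants, and the Discussion says recruitment for extremely small or ill neonates is delayed, so many scored events may precede randomization. If arm does not affect the score, adjustment is unbiased and may gain precision. This stands as a limit on size: zero bias is a real possibility, and no figure in the article supports any particular shift. It does not make the score a baseline value. Nor can an effect be excluded: the Background expects benefit to reach the child through maternal distress and behaviour, and the fifth session concerns feeding, though neither shows an effect on medical events in hospital.

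A second defence is that the rater is blind and works from the chart. That guards against assessor bias, which is not the issue here.

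A third is that the article gives the date of scoring and not the window of events scored. That is correct: counting events up to discharge is a reasonable inference from scoring at discharge with items on duration, but it is an inference.

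A reader might also infer that any post-randomization imbalance in NBRS, even by chance, biases the adjusted estimate. It does not; chance events after allocation weaken only the balance check.

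**Conclusion.** The inconsistency is plain on the article's own text: a score made at discharge is called baseline and is used where a pre-randomization value is needed. For the balance check the fault holds whether or not the programme affects the infant, because later events cannot be separated from allocation. For the adjusted models there is bias only if arm affects the NBRS and the NBRS is related to the outcome. Its size is unknown, from 0 to about 1.3 STAI points under the assumed shifts and slopes and a back-solved SD of about 11. The top of that range combines two upper-end assumptions and should carry little weight.

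It would be tempting to conclude that the trial's main result is compromised. The documents do not support that: the primary analysis is an unadjusted unpaired t-test, which the NBRS does not enter. The point concerns the baseline comparison and the secondary regressions for the primary and secondary outcomes. It deserves correction because the remedy is cheap, not because a large distortion has been shown.

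**What to change.** In Planned analyses, replace the discharge NBRS in both the balance check and the adjusted models with a severity variable fixed before randomization. Birthweight is the obvious choice, since eligibility already requires it. Report the discharge NBRS by arm as a descriptive result, or adjust for it only in a sensitivity analysis labelled as conditioning on a post-randomization variable.

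An alternative is an NBRS scored only from chart events before randomization. It is less certain: infants differ in age at enrolment, so items that count duration would partly reflect that age, and the validity evidence cited in the article is not shown to carry over to a truncated score. It should be used only if judged valid on those grounds.

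The change is a few words in the analysis text and needs no new data if birthweight is used. It leaves the primary analysis and sample size as they are. The price is some loss of prognostic information in the secondary model, by an amount the article does not allow one to estimate.

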Power analysis was based on the work of Mohide [52], which indicated that a change of 7 points on the STAI scale (the primary outcome) is considered clinically meaningful. Setting alpha = 0.05 and power = 0.8, we would need 40 subjects per group [53]. To account for attrition, a sample of 46 mothers per group will be recruited.

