### Procedures

The study timeline can be found in Figure 1. Following recruitment, informed consent is obtained, and baseline measures (STAI, PPQ, and EPDS) are administered. Participants are then randomized to either the Cues or the Care condition. Within a day of randomization, an intervener contacts the participant and arranges for the first session of the intervention.

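### The article calls maternal depression untestable because it is dichotomous, but the EPDS yields a graded 0–30 total and the dichotomy comes only from the cut point

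*Protocol article*

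**What the plan says.** In the protocol article, Additional variables lists the EPDS as one of two measures collected for exploratory analysis. It is a 10-item scale, and of its scoring the article says "The items are rated on a scale from 0 to 3, and refer to symptoms experienced in the past 7 days". Mothers scoring above a cut point of 12 are classified as at risk of a depressive disorder. The section closes with the reason for not testing: "Given that maternal depression is a dichotomous outcome, the sample size required to adequately test any related hypotheses would be prohibitive". It then concludes that hypotheses on depression, and on infant development, cannot be tested.

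The EPDS is collected on the same schedule as the anxiety score. Under Procedures, "baseline measures (STAI, PPQ, and EPDS) are administered" before randomisation; depression is measured again after the intervention, and the same self-report set is repeated at 6 months corrected age.

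For the primary outcome, the state score of the State-Trait Anxiety Inventory (STAI, 20 items rated 1 to 4), Planned analyses says "This is a continuous measure and will be analyzed using an unpaired t-test". The only sample-size calculation, under Participants, is for the STAI.

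**The concern.** The premise of the sentence does not match the instrument described just before it. Ten items scored 0 to 3 add up to a graded total, as the 20 STAI items do. The article treats the summed STAI score as continuous and says the secondary measures will be analysed likewise, yet it calls depression dichotomous. The dichotomy is a choice of endpoint, not a property of the data collected.

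This matters because the sentence covers any hypothesis about depression, not only hypotheses about the proportion at risk. A reader is told that sample size rules the question out, when part of that sample-size burden is created by cutting the score. A more efficient comparison is available from data already collected at three time points. The primary outcome, the listed secondary outcomes and the trial's sample size are not affected.

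**Working it through.** **Inputs from the article**
- Participants: "a change of 7 points on the STAI scale (the primary outcome) is considered clinically meaningful" and "Setting alpha = 0.05 and power = 0.8, we would need 40 subjects per group"; then "To account for attrition, a sample of 46 mothers per group will be recruited".
- Planned analyses: "The overall significance level will be considered at a two-sided 0.05 level".
- Additional variables: ten items, 0 to 3 each, cut point 12.

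**Inputs not in the article, so assumed**
- The standardised EPDS effect d: 0.3 to 0.63.
- The proportion of control (Care) mothers above the cut: 20% to 50%.
- A normally distributed score with equal variances, and 40 mothers analysed per arm.

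**Step 1. Range of the total.** 10 × 0 = 0 to 10 × 3 = 30.

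**Step 2. What 40 per group implies for the STAI.** The STAI SD is not given, so the figure can only be solved backwards:

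d = (1.960 + 0.842) × √(2/40) = 2.802 × 0.2236 = 0.626, so SD = 7 / 0.626 = 11.2 points.

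The noncentral-t version gives d = 0.634 and SD 11.0. On attrition, 1 − 40/46 = 13%, so 46 recruited is consistent with 40 analysed.

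**Step 3. Power of the EPDS total at 40 per arm.** Power = Φ(d√(n/2) − 1.960), with √(40/2) = 4.472.
- d = 0.626: Φ(2.802 − 1.960) = 80% (79% by t)
- d = 0.5: Φ(2.236 − 1.960) = 61%
- d = 0.4: Φ(1.789 − 1.960) = 43%
- d = 0.3: Φ(1.342 − 1.960) = 27%

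For 80% power these need 40, 63, 99 and 175 per arm.

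**Step 4. Power of the cut score for the same shift.** If a proportion p_c of controls lies above the cut, a downward shift of d gives p_t = 1 − Φ(z(1 − p_c) + d). With p̄ the mean of the two proportions and q = 1 − p,

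power = Φ{[(p_c − p_t)√n − 1.960√(2p̄q̄)] / √(p_c q_c + p_t q_t)}.

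Example with p_c = 20% and d = 0.626: p_t = 1 − Φ(0.842 + 0.626) = 7.1%. Then power = Φ[(0.129 × 6.325 − 1.960 × 0.484) / 0.475] = Φ(−0.28) = 39%.

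| Controls above cut (assumed) | Treated above cut at d = 0.626 | Power, cut, d = 0.626 | Per arm for 80%, d = 0.626 | Power, cut, d = 0.5 | Power, cut, d = 0.4 |
|---|---|---|---|---|---|
| 20% | 7.1% | 39% | 110 | 29% | 21% |
| 30% | 12.5% | 48% | 85 | 35% | 25% |
| 40% | 18.9% | 54% | 73 | 39% | 27% |
| 50% | 26.5% | 58% | 67 | 41% | 29% |
| Total score, uncut | – | 80% | 40 | 61% | 43% |

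Using d = 0.634 instead gives 40%, 49% and 55% in the first three rows.

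**Step 5. Reading the table.** In every row the cut score has less power than the total for the same shift. At d = 0.626, with 20–40% of controls above the cut, the cut multiplies the required number per arm by 110/40 = 2.75 down to 73/40 = 1.8.

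**The case against.** The sentence can be read as coherent. It calls maternal depression dichotomous, not the EPDS. The section presents the scale as a screen, with a cut point and with sensitivity and specificity against psychiatric diagnosis. Being at risk is a legitimate endpoint, and for that endpoint the working agrees that 40 per arm is too few. The article also labels depression exploratory, openly and more than once, and how an exploratory score is modelled may be set out in a fuller document.

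Much of this stands. The exploratory status is a fair choice, and the sample-size argument is right for the classified outcome. It does not rescue the reason as written. The sentence does not name the classified outcome, extends to all depression hypotheses, and gives the dichotomy as the sole ground. That is something the article states, not a detail it leaves out.

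A reader might go further in two ways that the article does not support:
- That the EPDS total has the same power as the STAI. This needs an equal standardised effect. The article gives no EPDS effect, SD or target difference, and the intervention is aimed at anxiety and sensitivity. With a smaller effect on depression, the total is underpowered too.
- That the trial throws the graded information away. The EPDS is kept for exploratory analyses, and nowhere does the article say that the total will be dropped or that only the cut will be reported.

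**Conclusion.** The concern holds in a limited form: the reason given for not testing depression is unsound, while the decision to keep depression exploratory is not. By the article's own description the score is graded, and the cut point creates the dichotomy.

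The cost of the cut, at an assumed effect near 0.63, is a fall in power from about 80% to about 40–55% at 40 per arm. These figures rest on carrying the back-solved STAI effect over to the EPDS, on assumed control proportions of 20–40%, and on a normal score. The direction holds at every effect size and control proportion tabulated; the size depends on inputs the article does not give. Whether the trial could adequately test depression on the total score cannot be settled from the article, and at effects of 0.5 or below it could not at the conventional 80%.

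**What to change.** - Compare the EPDS total as a continuous exploratory outcome after the intervention and at 6 months, adjusted for baseline EPDS and hospital (the stratification factor), and report the mean difference with a 95% CI. Baseline adjustment should add some precision; how much depends on a correlation the article does not give.
- Keep the proportion above the cut point as a descriptive summary.
- Reword the last paragraph of Additional variables so that the sample-size argument refers only to the classified outcome, and justify exploratory status by the absence of a power calculation for the EPDS.

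The cost is a change of wording plus one more reported exploratory comparison. No further data collection is needed.

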### Procedures

The study timeline can be found in Figure 1. Following recruitment, informed consent is obtained, and baseline measures (STAI, PPQ, and EPDS) are administered. Participants are then randomized to either the Cues or the Care condition. Within a day of randomization, an intervener contacts the participant and arranges for the first session of the intervention.

**Figure 1 F1:**
[figure not shown]
**Cues and Care Trial timeline**. STAI = State TraitAnxiety Inventory. EPDS = Edinburgh Postnatal Depression Scale. PPQ = Perinatal PTSD Questionnaire. PSS-NICU = Parent Stressor Scale: Neonatal Intensive Care Unit. BSID-III = Bayley Scales of Infant Development-third edition.

Post-intervention measures are administered at the participant's home 2 – 3 weeks after the intervention ends (when infants are 1 – 1.5 months corrected age). This assessment includes observation of mother-infant interaction, and completion of the self-report measures of anxiety, depression, and posttraumatic stress. In addition, participant mothers are asked to report on their satisfaction with the intervention that they received. A follow-up assessment of mothers and infants takes place at home when the infants are 6 months old (corrected age). At this time, the BSID-III is administered, in conjunction with observation of mother-infant interaction, and the completion of the same set of self-report measures used at baseline and at the immediate post-intervention assessment.

